### Statistical analysis

Data will be analysed on an intention to treat basis. The SPSS (IBM Corporation, Armonk, NY, USA) computer package will be used with a two-sided *p* value of < 0.05 taken as the level of significance. For feasibility outcomes, simple categorical data will be presented descriptively using mean (SD), median (IQR) for skewed data or *n* (%) for each group. Recruitment of a large trial within 18 months (based on rates observed in the pilot trial), and retention of 85% or better will be deemed acceptable.

Descriptive statistics (mean (sd) and *n* (%)) will be calculated for demographic and baseline characteristics of the patients. For the clinical outcome of SSI at 30 days, logistic regression analysis will be undertaken with SSI as the dependent variable and randomisation group as the independent variable. The model will be adjusted for confounding variables such as sex, age, BMI, smoking status, diabetes status and surgical site, as well as implant vs non-implant surgery. The regression model performance will be assessed by the Hosmer and Lemeshow test. Logistic regression will also be undertaken for satisfactory healing—total ASEPSIS score ≤ 10. For quality of life (EQ-5D-3 L and SF-36), an intragroup and intergroup analysis will be performed, using Friedman’s two-way analysis of variance (ANOVA) test to assess for intragroup differences, and Mann-Whitney *U* tests to assess for intergroup differences of the SF-36 responses. For the EQ-5D, responses will be dichotomised into ‘no problems’ and ‘problems’, and intragroup analysis conducted using related sample’s Cochrane’s Q test, with Pearson’s χ^2^ tests for intergroup analysis. For time to event data (time to return to work and mortality), Kaplan-Meier and long rank tests will be used to calculate and compare event rates between groups, followed by a cox regression to adjust for confounding variables.

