#### Feasibility outcomes

The measured effect size of the trial intervention, in order to contribute to the power calculation and design of a full scale RCTEligibility rates and reasons for non-eligibilityParticipant recruitment rates and reasons for non-recruitmentFollow-up and study retention rates and reasons for drop-out/non-attendanceFitness for purpose and acceptability of follow-up arrangementsThe suitability of the trial intervention in different wound types/areasThe suitability of the inclusion/exclusion criteriaThe suitability of outcome assessment measure(s)Fitness for purpose and acceptability of data collection methods, including the use of smartphone or online ‘apps.’Rates of participant withdrawal from the trial; participant response rates to questionnaires; likely rates of missing study data.

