### Sample size calculation

The incidence of SSI’s following clean and clean contaminated, non-implant surgery varies widely between the procedures to be included in this study. Whilst the overall infection rate is quoted as being 2.1–3.3%, this is predominantly based on the findings of Cruse and Foord [27] following their long-term surveillance. This has been criticised as it predominantly relies on questionnaire follow-up, over the phone at day 28 post-surgery. The reality in practice is that the infections rates are much higher and are more frequently diagnosed when examined by a blinded observer [28].

The power calculation is based on the primary endpoint having a 90% power and 5% significance. A non-randomised prospective trial comparing Leukomed® Sorbact® with standard dressings in non-implant, clean or clean-contaminated vascular surgery patients, carried out in the same centre demonstrated an overall reduction in SSI from 19 to 10% [29]. To demonstrate the same reduction in SSI, a sample size of 320 per group, or a total of 712 patients, allowing for a 10% loss to follow-up, is required. Study retention rates will be examined at the first interim analysis, and the power calculation amended accordingly. With such a large sample size, there is a high potential for larger loss to follow-up rates than initially expected. Therefore, this pilot study will aim to recruit one-fifth (144) of the total patients needed. The results of this pilot trial, along with other published data on DACC in the reduction of SSI, will be combined to produce a final power calculation for a full-scale RCT.

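### The planned adjusted logistic model has at least 8 slopes for about 18–21 expected infections, so its treatment estimate will be unstable and, on average, modestly too far from the null

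*Protocol article*

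**What the plan says.** The Statistical analysis section of the protocol article specifies one between-arm analysis of 30-day SSI: a logistic regression with randomised group as the independent variable. It then says: "The model will be adjusted for confounding variables such as sex, age, BMI, smoking status, diabetes status and surgical site, as well as implant" versus non-implant surgery. No coding is given for smoking status or surgical site, and neither a limit on covariates nor penalisation is mentioned. The fit check is named: "The regression model performance will be assessed by the Hosmer and Lemeshow test". Return to work and mortality are to be analysed by Kaplan-Meier and log-rank methods, "followed by a cox regression to adjust for confounding variables".

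Under Feasibility outcomes, the first item is "The measured effect size of the trial intervention, in order to contribute to the power calculation" and design of a full-scale trial. The Sample size calculation section takes its rates from a non-randomised study in the same centre that "demonstrated an overall reduction in SSI from 19 to 10"%, sets the pilot at 144 patients, and says that the pilot result will be combined with other published data for the final power calculation.

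**The concern.** A maximum-likelihood logistic model with about two events per coefficient is poorly behaved. Its coefficients are on average too far from zero, their spread grows, and in some samples a covariate pattern separates the outcome so that no finite estimate exists. The Hosmer–Lemeshow test, usually run on ten risk groups, has too few events per group to show misfit. An adjusted Cox model for deaths meets the same difficulty if deaths are few.

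The effect estimate is one of the pilot's stated products. If the adjusted odds ratio were the figure carried forward, the full trial's design would rest on a noisier and slightly optimistic number. The plan calls the covariates confounders, but randomisation already balances them in expectation. Here adjustment can only offer some precision and protection against chance imbalance.

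**Working it through.** **Inputs.** From Sample size calculation: SSI 19% and 10%, pilot N = 144, 10% loss, and "The power calculation is based on the primary endpoint having a 90% power and 5% significance". From Randomisation: equal allocation. From Statistical analysis: a "two-sided *p* value of < 0.05 taken as the level of significance", retention of 85% or better deemed acceptable, and the covariate list.

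**The plan's own figure.** Two proportions, pooled variance, two-sided 5%, 90% power:

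n = [1.960 × √(2 × 0.145 × 0.855) + 1.282 × √(0.19 × 0.81 + 0.10 × 0.90)]² / 0.09² = 319.6, so 320 per group.

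With 10% loss, 320 / 0.9 = 355.6, so 356 per group and 712 in total. This matches "a sample size of 320 per group, or a total of 712 patients, allowing for a 10% loss to follow-up, is required". One-fifth of 356 is 71.2, or 72 per arm, which gives 144.

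**Expected infections** = N × (0.19 + 0.10) / 2.

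| Analysed N | Infections | Per slope, 8 slopes | Per slope, 10 slopes |
|---|---|---|---|
| 144 | 20.9 | 2.6 | 2.1 |
| 129.6 (10% loss) | 18.8 | 2.3 | 1.9 |
| 122.4 (15% loss) | 17.7 | 2.2 | 1.8 |

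**Slopes.** Group, sex, age, BMI, smoking, diabetes, surgical site and implant make 8 if each takes one degree of freedom. Ten assumes three levels each for smoking and surgical site. That coding is an assumption.

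**Simulation.** True marginal log-OR = ln[(0.10/0.90) / (0.19/0.81)] = −0.747. Covariate distributions were assumed, with a log-OR of 0, 0.2 or 0.4 per covariate and 2,000 to 6,000 replicates per scenario. Bias is measured against each model's own target (conditional or marginal). Failed fits are excluded from the averages. Ranges run over the three covariate strengths.

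| N, slopes | Adjusted: excess | Adjusted: SD | Adjusted: failed fits | Unadjusted: excess | Unadjusted: SD |
|---|---|---|---|---|---|
| 144, 8 | 9–16% | 0.60–0.62 | 0.4–1.5% | 3–7% | 0.54–0.55 |
| 144, 10 | 14–15% | 0.60–0.64 | 2.5–2.9% | about 5% | 0.53–0.55 |
| 130, 8 | 15–16% | 0.64–0.68 | 0.8–2.1% | 6–7% | 0.58 |
| 130, 10 | 17–19% | 0.64–0.72 | 3.8–5.7% | 5–7% | 0.56–0.59 |

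The unadjusted model failed in at most 0.2% of runs. Firth's penalised likelihood with the full covariate set came within about 2% of its target throughout. Similar runs under other assumptions gave 12–16% (8 slopes) and 16–21% (10–11 slopes, N = 130 and 122) adjusted, and 2–8% unadjusted.

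**Bias against noise.** At N = 130 with 10 slopes and null covariates, the bias is 0.885 − 0.747 = 0.138, and 0.138 / 0.641 = 0.22 of an SD. With a log-OR of 0.2 per covariate, a single estimate lay beyond the truth in 55–57% of replicates. Centred on the true odds ratio of 0.47, the approximate 95% sampling range is exp(−0.747 ± 1.96 × 0.641) = 0.13 to 1.66 adjusted, and exp(−0.747 ± 1.96 × 0.561) = 0.16 to 1.42 unadjusted.

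**Hosmer–Lemeshow.** Ten groups share 17.7–20.9 infections, about 2 per group on average.

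**Mortality.** The protocol gives no death rate. If it were 2–5%, 144 × 0.02 = 2.9 and 144 × 0.05 = 7.2, so about 3–7 deaths.

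**The case against.** The strongest case against has five parts.

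- **The bias is small next to the noise.** This stands. It is an average of at most about a fifth of an SD, and part of it is present without adjustment. A reader might infer that the pilot's odds ratio will be exaggerated. The figures support only a tendency, since a single estimate is beyond the truth only slightly more often than not.
- **The harm to the full trial is not in the text.** This stands. A reader might infer that an inflated odds ratio will make the full trial too small. For scale, a log-OR inflated by 10–19%, applied alone to a 19% control rate in the plan's formula, would give about 272 down to 239 per group instead of 320, with true power of about 85% down to 80%. But the protocol does not say that the adjusted odds ratio is used, its existing calculation uses two proportions, and it will combine the pilot with other published data.
- **The number of parameters is not stated.** This stands against a firm count of ten or more. Eight is the minimum that the named terms allow, and the conclusion does not need more.
- **Covariates and coding may be settled in an analysis plan that is not shown.** This stands in part. Coding can be left to that plan, but the article itself names the model, the covariates and the fit test, and offers no other between-arm SSI analysis.
- **Dropping covariates is not required.** This stands. Firth's method copes with the full set. No stratification is described under Randomisation, so chance imbalance in site or implant status is possible.

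The event count is also uncertain. The 19% and 10% come from non-implant patients, while the pilot includes implant patients and also admits CDC-defined SSI. Yet with both arms at 19% and 10% loss, 129.6 × 0.19 = 24.6 infections, still only about 3 per slope with 8 slopes.

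**Conclusion.** The point holds in a moderate form. On the protocol's own rates the pilot expects about 18–21 infections for a model with at least 8 slopes. The unpenalised adjusted estimate will be less precise than the unadjusted one, will occasionally fail to exist, and will be on average about 10–19% too far from the null on the log-OR scale, against about 2–8% unadjusted. The size of the bias rests on assumed covariate distributions, effects and coding. The event count rests on rates from a non-implant cohort.

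The documents do not support saying that the estimate is certain to be exaggerated or that the full trial will be undersized. Nor do they show the Cox plan to be wrong as a whole: it also covers return to work, which may have many events, and the mortality difficulty depends on an assumed death rate. What remains is a model that is too large for the data, with no statement of which estimate goes forward to the full trial.

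**What to change.** - Report SSI as n (%) by arm with the unadjusted risk difference and odds ratio and their 95% CIs. Name this as the pilot estimate that informs the full trial.
- Keep any adjusted analysis as a sensitivity analysis, with either a short covariate list fixed in advance or Firth's penalised likelihood.
- Do not rely on the Hosmer–Lemeshow test at about 2 events per decile.
- If deaths are few, report mortality as n (%) by arm instead of an adjusted Cox model. Leave the Cox model for return to work as planned.

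The cost is a change of wording in the analysis section or the analysis plan, with no change to data collection. The downside is that the main pilot estimate gives up a small possible gain from adjustment, including for chance imbalance. The unadjusted estimate will also remain imprecise, so its confidence interval should be carried into the full-trial planning along with the point estimate.

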### Quality of life assessments

The EQ-5D questionnaire is a widely recognised and validated generic measure of health-related quality of life. This questionnaire has been assessed for acceptability and validity in a number of patient groups [23, 24]. The SF-36 has been well-validated in a variety of UK populations [25, 26]. It measures eight domains which can be used to calculate summary physical and mental component scores.

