### Study visits

Following screening and informed consent, a baseline visit will take place to record demographic data and medical history, prior to randomisation. Study visits will take place between post-op days 5 and 7, at post-op day 30 and at 6 months. Patients will be contacted both by post and telephone when arranging follow-up in order to maximise retention. At the study visits, information such as antibiotic use, length of hospital stay, visits to the general practitioner, dressing changes/number of dressings used and return to work or daily activities will be recorded by a non-blinded study nurse or doctor. Patients will be deemed to have returned to normal activities if they have returned to work (if they are of working age) or if they have returned to their pre-operative activity levels. In particular, patients will be asked if they have returned to driving, exercise or previous levels of social activity.

The same individual will remove the dressing in situ and dispose of it in an opaque bag. A second assessor, blinded to the dressing type, will be invited into the room in order to score the wound on the ASEPSIS scale. This will be recorded in the CRF. With the dressing removed, anonymous photographs will be taken of the wound, to be reviewed by an assessor not involved in trial recruitment or follow-up and used for the standardisation of ASEPSIS scores between participants. With the blinded assessor out of the room, the first study nurse or doctor will replace the dressing. Postal quality of life questionnaires will be sent to participants at 3 months and 6 months. Table 1 outlines the schedule of assessments.

**Table 1 Tab1:** Schedule of assessments (SPIRIT figure)

Visit	1	2	3	4	5	–	–
	Screening	Baseline assessment	Day 0- day of surgery	Day 5–7 post op	Day 30 post op ± 3 days	3 Months post-op ± 7 days	6 Months post-op ± 7 days
Screening questionnaire	X						
Patient information sheet	X						
Informed consent		X					
Baseline questionnaire		X					
SF-36		X		X	X	X	X
EQ-5D-3 L		X		X	X	X	X
GP letter		X					
RANDOMISATION FORM			X				
HPA surgical wound healing post discharge questionnaire					X		x
Clinical review of wound				X	X		X

*SF36* short form 36 utility, *EQ*-*5D* EuroQoL 5 domain utility index, *HPA* health protection agency

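### Quality of life is compared between arms without using the baseline scores collected, alongside within-arm tests that cannot show a dressing effect

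*Protocol article*

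**What the plan says.** In the protocol article, *Statistical analysis*, the plan for EQ-5D-3L and SF-36 is that "an intragroup and intergroup analysis will be performed".

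- **SF-36:** Friedman's test within each arm, and between arms Mann-Whitney "tests to assess for intergroup differences of the SF-36 responses".
- **EQ-5D:** "responses will be dichotomised into ‘no problems’ and ‘problems", then Cochran's Q within each arm and Pearson's chi-square between arms.
- **Threshold:** the section sets one general rule, a "two-sided *p* value of < 0.05 taken as the level of significance". It names no lead quality-of-life score, no lead visit and no control of multiplicity.

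Three other places bear on this. Table 1, under *Study visits*, schedules both questionnaires at baseline and at four post-operative times; *Secondary outcomes* lists the same four times. *Quality of life assessments* says of the SF-36: "It measures eight domains which can be used to calculate summary physical and mental component scores". The footnote to Table 1 expands EQ-5D as "EuroQoL 5 domain utility index".

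Elsewhere in *Statistical analysis*, the logistic model for infection and the Cox regression for time-to-event outcomes are both adjusted for patient characteristics. The quality-of-life comparison is not.

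**The concern.** The comparison that matters is DACC against control. The tests named for it take no baseline value, so they forgo precision that could be had from data already scheduled for collection. Rank and chi-square tests also do not, as named, produce a between-arm difference with a confidence interval.

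The within-arm tests answer a different question: whether scores change over time. After surgery they are expected to change in both arms whatever the dressing. Printing a p-value for each arm invites the reader to treat significance in one arm and not the other as evidence for the dressing, which it is not.

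Dichotomising EQ-5D-3L merges its two worse levels, so a move between them is not seen. With no lead score or visit, an isolated p-value below 0.05 among many would be hard to interpret.

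**Working it through.** The document states no number of quality-of-life tests, so there is no figure of its own to reproduce here.

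**Inputs from the document.** SF-36: 8 domains and 2 summary scores. EQ-5D: 5 items. Post-operative times: 4, or 5 assessments with baseline. Two-sided alpha: 0.05. Pilot size: 144 with equal allocation, so 144/2 = 72 per arm.

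**Inputs assumed.** The baseline-to-follow-up correlation r, the within-arm power, the questionnaire response rate and the standardised effect. The document gives none of these.

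**1. Number of between-arm tests** = (SF-36 scores + EQ-5D items) × time points. Expected false positives if the arms do not differ = tests × 0.05.

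| SF-36 scores tested | Time points | Tests | Expected false positives |
|---|---|---|---|
| 2 summaries | 4 | (2+5)×4 = 28 | 1.4 |
| 8 domains | 4 | (8+5)×4 = 52 | 2.6 |
| all 10 | 4 | (10+5)×4 = 60 | 3.0 |
| 8 domains | 5 | (8+5)×5 = 65 | 3.25 |
| all 10 | 5 | (10+5)×5 = 75 | 3.75 |

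The expected count does not require independent tests. A family-wise rate does: 1 − 0.95^60 = 95.4% for 60 independent tests is only an upper guide, because the scores are correlated. Within-arm tests would add 2 × (8+5) = 26 to 2 × (10+5) = 30 p-values if domains are tested.

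**2. What within-arm tests can show.** Suppose the arms do not differ and each within-arm test has power w to detect change over time. The chance that exactly one arm is significant is 2w(1 − w): 2 × 0.5 × 0.5 = 50% at w = 0.5, and 2 × 0.8 × 0.2 = 32% at w = 0.8.

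**3. Value of the baseline score.** In a linear model, adjustment multiplies residual variance by 1 − r²:

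- r = 0.3: 1 − 0.09 = 0.91
- r = 0.5: 1 − 0.25 = 0.75
- r = 0.7: 1 − 0.49 = 0.51

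As an illustration, take an assumed standardised effect of 0.4, 65 per arm (72 × 0.9 = 64.8) and normal scores. Adjusted power is Φ(0.4/√(2(1 − r²)/65) − 1.96), which gives 67%, 75% and 89% at those three correlations. The Mann-Whitney test on the raw score has 61%, by multiplying the unadjusted signal 0.4/√(2/65) by √(3/π).

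**4. Missing questionnaires.** Friedman and Cochran's Q need every time point. If non-response is independent between visits, the fraction with all four follow-ups is 0.95⁴ = 81% at 95% response per visit and 0.90⁴ = 66% at 90%. This applies to the within-arm tests only.

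**The case against.** Rank tests are a reasonable choice for bounded, skewed scores with about 72 patients per arm, and a linear model brings assumptions that they avoid. Quality of life is one of several secondary outcomes in a feasibility pilot. Naming a test does not stop the investigators from also reporting medians, differences or intervals. All of this is fair, and it limits the weight of the point. It does not remove it: the article fixes these four tests, and none of those between arms takes a covariate.

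Several stronger readings are tempting, and the document does not support them.

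- **That the plan produces a fixed number of p-values, such as 60.** That is one entry in the table above. The article does not say which SF-36 scores or visits are tested; it says only that summary scores can be calculated.
- **That baseline data go wholly unused.** Baseline may enter Friedman and Cochran's Q as a time point, though these do not compare arms. Change scores between arms are not excluded either, but the text speaks of responses and mentions no change score.
- **That anyone missing a questionnaire drops out of the arm comparison.** Mann-Whitney and chi-square at a visit use everyone who answered at that visit. If the same patients miss several visits, the loss in the within-arm tests is also smaller than the figures in step 4.
- **That the main trial is left without a basis for its size.** *Sample size calculation* sizes it on infection, 19% against 10%.
- **That a planned utility outcome was discarded.** The index appears only in an abbreviation footnote, which calls the SF-36 a utility as well. *Secondary outcomes* names the questionnaires and no index.

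**Conclusion.** The point holds as a matter of method. The planned between-arm comparison takes no account of the baseline questionnaires, reduces EQ-5D-3L to two categories, and stands beside within-arm tests that cannot show a dressing effect. Because no score or visit is given priority, some 28 to 75 between-arm p-values are possible, with 1.4 to 3.75 expected below 0.05 by chance. That range depends on which scores and visits are tested.

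The precision forgone depends on correlations that the document does not give: a residual variance factor of 0.91 to 0.51 for r from 0.3 to 0.7. The formula is for a continuous score in a linear model and does not carry over directly to dichotomised items.

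The consequence is confined to the interpretation and precision of a secondary outcome. The infection outcome, the recruitment criterion, the 85% retention threshold and the main-trial sample size are untouched.

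**What to change.** For the SF-36 physical and mental summary scores and an EQ-5D-3L index, fit one repeated-measures model each, with arm, time, arm × time and the baseline value as terms, using all available visits. Report the between-arm difference with a 95% confidence interval, with a bootstrap interval if scores are skewed.

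Three models over four visits still give 3 × 4 = 12 contrasts, so name one lead visit for each score in advance and present the others as supportive. Report individual SF-36 domains, EQ-5D items at all three levels, and within-arm change descriptively, without p-values.

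The cost is a change of wording, the choice of an EQ-5D value set, and a modelling assumption in place of rank tests. No new data are needed, and the model is available in SPSS, the package already named.

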## Introduction

The Centres for Disease Control and Prevention (CDC) defines a surgical site infection (SSI) as an infection within 30 days of an operation or up to 90 days if an implant is left in place and the infection is related to an operative procedure [1]. SSI’s occur in at least 5% [2] of patients and have a significant impact on patient morbidity, mortality and have subsequent time and cost implications [3].

Microorganisms causing SSI’s may be either endogenous (present on the patient) or exogenous (from the environment). The most common bacteria causing a superficial wound infection are those which are present on the skin of the patient. Deeper wound infections may be due to contamination of the wound by bacteria encountered during a procedure. Despite the reported incidence of SSI’s for clean surgery of 2.1% [4], the incidence in practice varies significantly. Open varicose vein surgery has an incidence of SSI’s reported in the literature which varies from 1.5 to 16% [5, 6] whilst figures from the surgical site infection surveillance demonstrated a high rate of SSI’s in patients undergoing lower limb amputation (13.1%) [7]. Conversely, SSI rates following carotid endarterectomy are reported as low as 0.2% [8, 9].

The Sorbact® range of dressings contains dialkylcarbamoylchloride (DACC), found in a spider’s web, which mediates the irreversible binding of bacteria that exhibit a high cell surface hydrophobicity (CSH). Large numbers of adherent or ‘trapped’ bacteria can then be removed from the wound at each dressing change. They are removed without disrupting the bacterial cell wall, thereby avoiding the resultant increase in inflammation observed with traditional antibiotics or antiseptics [10]. Numerous bacteria and fungi that exhibit CSH have been shown to attach to the DACC-coated material, including *Staphylococcus aureus*, *Pseudomonas aeruginosa*, *Enterococcus faecalis*, *Candida albicans* and the dermatophyte *Trichophyton rubrum* [11, 12].

DACC-coated dressings are available on the open market in both the UK via the National Health Service (NHS) supply chain, and the USA [13].

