#### Secondary outcomes

Secondary outcomes will be:The incidence of SSI—total ASEPSIS score ≥ 21 or SSI as defined by CDC definitions—at 90 days for implant patients only (as per the CDC definition for SSI in implant-involving surgery)Satisfactory healing—total ASEPSIS score ≤ 10—at 30 days post-surgery for non-implant surgery and implant patientsSatisfactory healing—total ASEPSIS score ≤ 10—at 90 days for implant patients onlyQuality of life: using EurolQol 5 Domains (EQ-5D-3 L) and Short Form 36 (SF-36) v2 questionnaires at 5–7 days, 30 ± 3 days, 3 months ± 7 days, and 6 months ± 7 days.Time to return to normal activity/work (measured in working days between the day of surgery and the day the patient returned to work).Resource use—primary care visits, requirement for antibiotics, readmission, re-intervention within 30 days and 6 months.30-day mortality.

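### Time to return to work is to be estimated by Kaplan-Meier with no place for death before return; if such deaths are censored, the proportion returned is overstated, by little at low mortality

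*Protocol article*

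**What the plan says.** The Statistical analysis section gives one method to two outcomes, return to work and mortality: it states for both that "Kaplan-Meier and long rank tests will be used to calculate and compare event rates between groups". A Cox model comes after these, with the aim of adjusting for confounders. Neither the regression nor the estimator is described as cause-specific or as allowing for competing events.

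Under Secondary outcomes, time to return to normal activity or work is "measured in working days between the day of surgery and the day the patient returned to work". Study visits widens this for people not of working age, who count as returned "if they have returned to their pre-operative activity levels". Neither place says what happens to a patient who dies before returning.

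Death is foreseen: the Secondary outcomes list includes "30-day mortality", and mortality is analysed as a time-to-event outcome in the same sentence as return to work. The Recruitment section admits semi-elective and emergency patients. Trial timescales sets follow-up at six months. The article states no expected mortality and no expected return rate.

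**The concern.** Kaplan-Meier handles two states: the event has happened, or the patient is censored and could still have it. Death before return fits neither. If the patient is censored at death, the estimator treats that person as still able to return and passes the person's weight to those who remain at risk. One minus Kaplan-Meier then describes return in a population in which nobody dies. It is never below the proportion who actually return, and it is above it whenever someone dies while others return later. The median time to return is pulled earlier for the same reason.

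This matters because the section uses Kaplan-Meier to calculate event rates as well as to compare them, and the calculated rate is the quantity affected. If death rates differed between arms, the overstatement would be larger in the arm with more deaths.

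**Working it through.** **The plan's own figures.** The article states no figure for return to work or for mortality. Its only calculation concerns SSI: 19% against 10%, 90% power, two-sided 5%. With pooled variance, n = [1.960·√(2·0.145·0.855) + 1.2816·√(0.19·0.81 + 0.10·0.90)]² / 0.09² = 319.6, so 320 per group, and 640/0.9 = 711.1, so 712. Both reproduce, but they do not bear on this point. The pilot size does: 144 patients, equally allocated, is 72 per arm.

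**Assumptions (not in the article).** True proportion returned by six months R = 70%, with 50% and 80% as a range; constant hazards of return (h) and death (d) over six months taken as one unit of time; deaths censored.

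**Standard error.** √(0.70·0.30/72) = 5.4 points per arm. It is 5.9 points at R = 50% and 4.7 at R = 80%.

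**Case A: the input D is the share who die before returning.** The total hazard is −ln(1 − R − D), and return takes the share R/(R + D) of it. For D = 5%: −ln(0.25) = 1.3863; h = 1.3863·0.70/0.75 = 1.2939; 1 − e^(−1.2939) = 72.6%, an excess of 2.6 points.

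**Case B: the input M is all-cause six-month mortality, with the same death hazard continuing after return.** Here d = −ln(1 − M), and h solves h/(h + d)·(1 − e^(−(h+d))) = R. For M = 5%: d = 0.0513, h = 1.2531, and 1 − e^(−1.2531) = 71.4%, an excess of 1.4 points. Only about 2.9% die before returning in this case.

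Excess of one minus Kaplan-Meier over the true 70%, in points (and in per-arm standard errors):

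| Input percentage | Case A: die before return | Case B: all-cause mortality |
|---|---|---|
| 3% | 1.5 (0.28) | 0.9 (0.16) |
| 5% | 2.6 (0.48) | 1.4 (0.27) |
| 10% | 5.5 (1.03) | 2.9 (0.54) |

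The two columns must not be confused. Under this model, D = 5% in Case A corresponds to all-cause six-month mortality of 8.8% (d = 1.3863 − 1.2939 = 0.0924; 1 − e^(−0.0924) = 8.8%).

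**Other return rates.** At an input of 5%, Case A gives 1.6 points for R = 50% and 3.2 for R = 80%; Case B gives 1.1 and 1.5.

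**Bounding case.** If every death precedes every return, one minus Kaplan-Meier is R/(1 − D). For D = 5% this is 0.70/0.95 = 73.7%, an excess of 3.7 points.

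**Simulation (144 patients, constant hazards, inputs as in Case A).** With deaths censored, the estimate was 61.9% against a true 59.9% with 5% deaths, and 64.4% against 60.0% with 10%. With deaths kept at risk as not returned to the end of follow-up, the estimate equalled the true value in both.

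**Between arms.** With true return of 60% in both arms and equal deaths, the difference in estimated rates is unbiased. With 5% dying before return in one arm and 10% in the other, a false difference of about 2.3 points appears, in favour of the arm with more deaths.

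**The case against.** The strongest reply is that the article never says deaths are censored. An analyst could keep a patient who dies as not returned to the end of follow-up, and Kaplan-Meier would then carry no bias from death. Censoring rules are often left to an analysis plan or full protocol, neither of which is shown. This stands to the extent that the overstatement is conditional. A reader might infer that the reported return rate will be too high, and the article does not support that. What remains is that the article has already named the estimator for this outcome, and applying it in the ordinary way, with nothing to steer the analyst elsewhere, gives the overstated rate.

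A reader might also infer that the trial includes amputees, and so expect high mortality and slow return. The Introduction mentions "patients undergoing lower limb amputation" only when citing a background infection rate. The eligibility criteria neither list amputation nor exclude it. The point does not need it.

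Three further objections stand. With deaths censored, the log-rank test and Cox model still compare cause-specific hazards validly; they simply do not address the proportion who return. Bias between arms needs different death rates under two wound dressings, and the article gives no reason to expect that. Finally, this is a secondary outcome of a 144-patient pilot whose stated acceptability criteria are recruitment and retention, so no stated decision depends on the return curve.

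**Conclusion.** The point holds in conditional form. Kaplan-Meier is poorly suited to the proportion returning to work or normal activity when death can come first, and under conventional censoring it overstates that proportion. The size cannot be derived from the article and rests on the assumed return rate, mortality and constant hazards. At 70% return and all-cause six-month mortality of 3 to 10%, the excess is 0.9 to 2.9 points, or 0.16 to 0.54 of a per-arm standard error. It reaches 5.5 points, about one standard error, only if 10% die before returning. The fault lies in the estimated rate, not in the validity of the log-rank or Cox comparison. It is minor at low mortality but inexpensive to correct.

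**What to change.** In the Statistical analysis section, separate the two outcomes. Keep Kaplan-Meier for mortality. For time to return to work or normal activity, report the cumulative incidence of return with death as a competing event (Aalen-Johansen estimate), with Gray's test if proportions are to be compared. Alternatively, keep patients who die as not returned to the end of follow-up; this gives the same estimate when the only other censoring is at that common end. Censor only at withdrawal, loss to follow-up or the end of follow-up, and label any Cox model for this outcome cause-specific.

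The horizon for the curve should be stated at the same time, because Trial timescales gives six months whereas Trial exit and the adverse event reporting period refer to one year.

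The cost is a sentence or two. Mortality is already an outcome, so no new data should be needed. The reported return rate will be slightly lower than under censoring, and the cumulative incidence routine may lie outside the base SPSS menus; keeping deaths as not returned avoids that.
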